### Sample size

The trial is powered to detect a difference of five points on our primary outcome (the PCS score of the SF-36 at 6 months following recruitment) between the intervention and control groups. In a previous study, we found that mean PCS at 6 months after hospital discharge was 34 with a SD of 10.^19^ This SD is similar to that reported at 6 months in 110 participants in the standard limb of the PRaCTICal UK 20 follow-up study (SD 11.7), and in a follow-up study of 252 critically ill patients in The Netherlands (SD 11.2).^21^ Taking a SD of 11, a five-point difference would give a medium effect size of 0.45. A sample size calculation based on a power of 80% to detect a five-point difference in SD at a significance level of 0.05 would require 77 participants in each group, a total of 154 for the trial. However, the 6-month mortality in this group of patients is known to be approximately 40%. In addition, we anticipate that we may lose a further 10% of participants to follow-up for other reasons. We will therefore need to recruit a total of 308 participants (154 in each group).

### Randomisation

Participants will be randomised in a 1:1 ratio, using permuted random block allocation, to either intervention or control group. The randomisation process will be administered centrally by Newcastle Clinical Trials Unit via a secure web-based system. Randomisation will be stratified by admitting Critical Care Unit, type of admission (surgical or medical) and the participant's prehospitalisation activity level. We will use Katz's ADL Index^22^ to stratify participants into either ‘low’ activity (score of 0–3) or ‘high’ activity (score of 4–6).

### Blinding

Owing to the nature of the intervention, it is not possible to blind the participants, clinical staff or research staff to the treatment group. However, the outcome assessments at hospital discharge, and at 3 and 6 months after randomisation, will be undertaken by a research nurse who will be blinded to the treatment group. To avoid accidental unblinding, patients attending for assessment will be requested not to reveal their treatment group to the research nurse.

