#### Secondary outcome measures

Mental health: the SF-36 Mental Component Summary (MCS) score.

Exercise capacity: the 6 min walk test.^13^

Muscle power: hand grip and quadriceps muscle strength using a dynamometer^14^ (see online supplementary appendix S1).

Physical functional ability: measured at Critical Care discharge using the Modified Rivermead Mobility Index.^15^

Activities of daily living (ADLs): ability to perform ADLs will be assessed using the Functional Independence Measure (FIM).^16^ The FIM and other questionnaires may be completed via a telephone call, rather than in person, at the 3-month and 6-month follow-up visits.

QoL: SF-36 and EQ-5D questionnaires will be administered to assess participants’ QoL. Utility values will be derived from the EQ-5D and from the SF-36 using the algorithm provided by the SF-6D.^17^ These will be used as the outcome measures in the economic analysis.

Outcome and location: survival status and place of residence will be recorded at hospital discharge, and 3 and 6 months following randomisation.

Delirium: before beginning rehabilitation, participants will be screened for delirium using the Confusion Assessment Method for the Intensive Care Unit.^18^

Ventilator-free days: defined as the number of days from randomisation (day 1) to day 28 on which a patient breathed without mechanical ventilation (includes non-invasive ventilation) if the period of unassisted breathing lasted at least 48 consecutive hours. Continuous positive airways pressure is considered to be unassisted breathing.

Health economic outcomes: utility scores will be generated using the SF-6D algorithm and the EQ-5D scores. Patient costs for hospital visits will be assessed at 6 months, using the Patient Costs Questionnaire (see online supplementary appendix S2).

The time schedule of assessments of participants is shown in table 1.

**Table 1 BMJOPEN2015008035TB1:** Schedule of data collection and outcome assessments

	Randomisation	Rehabilitation sessions	Critical Care discharge	Hospital discharge	3 Months from enrolment	6 Months from enrolment
Demographic and diagnostic data	X					
Severity of illness: APACHE II score	X					
Premorbid activity	X					
Sedation hold		X				
Safety screen		X				
Session duration		X				
Session milestones		X				
Adverse events		X				
Quality of life: SF-36 and EQ-5D				X	X	X
Six-minute walk test				X	X	X
Functional Independence Measure			X	X	X	X
Grip strength, both hands			X	X	X	X

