### Data collection

The study data collected at each time point are summarised in table 1. All participating units contribute data to the Intensive Care National Audit and Research Centre (ICNARC) case mix programme. Data collected routinely by units as part of this national audit will be used to provide demographic, diagnostic and severity of illness data for participants. These data will include: age; gender; admission diagnoses; Acute Physiology and Chronic Health Evaluation (APACHE) II severity of illness score; number of organ failures; admission and discharge location; length of stay (in Critical Care and in hospital); status on hospital discharge; and ultimate discharge location. An estimate of each participant's premorbid functional ability (Katz's ADL Index) will be made by interview with their next of kin. For each day a participant remains in Critical Care, we will record the type and total dose of sedatives and the total calorie intake received as enteral or parenteral nutrition. Data related to each physiotherapy session will be collected by the physiotherapist allocated to that session, under the supervision of the research physiotherapist. We will assess participants at discharge from Critical Care against the Modified Rivermead Mobility Index. At hospital discharge, 3 and 6 months after study enrolment, patients will be invited to attend a follow-up appointment where the study assessments will take place. Where feasible, appointments will coincide with routine clinical follow-up, to enhance the likelihood of good compliance. Participants who do not attend their appointment will be followed up by telephone.

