## Analysis

### Statistical analysis

The PCS component of the SF-36 at 6 months following recruitment is the primary end point of the study. In order to test the primary hypothesis of no difference between the intervention and control groups, the principal analysis will examine the difference between the groups on this measure using Analysis of Covariance (ANCOVA) in order to adjust for the effects of covariates in the analysis. The normality of the outcome variable will be assessed and, if necessary, transformations considered although ANCOVA are robust to deviations from this distribution. The covariates to be considered will include stratification variables (unit, admission type and preadmission activity level) in addition to demographic variables such as age and gender. More basic illustrative analyses using the t test or non-parametric alternatives may also be undertaken while, in addition, summary statistics will be calculated.

A broadly similar approach will be used to analyse the secondary outcome measures (the MCS component of the SF-36, the 6 min walk test, FIM, grip strength, quadriceps strength and body mass index (BMI)) at both 3 and 6 months post-study entry, in addition to at hospital discharge. Additionally, the 3-month and hospital discharge data on the PCS component of the SF-36 will be analysed in this fashion, along with the FIM, grip strength and BMI outcomes at Critical Care discharge. Repeated measures methods (again based on analysis of variance) will be employed in order to examine these outcome measures longitudinally across collected time points. Standard survival data methods, such as Kaplan-Meier and the log rank test, will be used to compare survival between the groups at 3 and 6 months. We will also compare durations of Critical Care and hospital stay, in addition to the delirium and ventilator-free days measures.

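### The stated assessor blind does not cover Critical Care discharge, where the only Modified Rivermead reading and the first FIM, grip and quadriceps readings are taken

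*Protocol article*

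**What the plan says.** The Blinding section of the protocol article starts from the position that "it is not possible to blind the participants, clinical staff or research staff to the treatment group". It then makes one exception: "the outcome assessments at hospital discharge, and at 3 and 6 months after randomisation, will be undertaken by a research nurse who will be blinded". That exception names three visits.

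Table 1 schedules outcome measures at a fourth visit, Critical Care discharge: FIM, grip strength, quadriceps strength, BMI and the Modified Rivermead Mobility Index. The secondary outcomes list gives the last of these as "Physical functional ability: measured at Critical Care discharge using the Modified Rivermead Mobility Index", and Table 1 shows it at no other visit. The Data collection section says "We will assess participants at discharge from Critical Care against the Modified Rivermead Mobility Index" and names no assessor.

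The Statistical analysis section sets out covariate-adjusted comparisons at hospital discharge, 3 months and 6 months. It adds further comparisons, "along with the FIM, grip strength and BMI outcomes at Critical Care discharge". It then plans repeated-measures methods for these outcomes over every visit at which they were collected.

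**The concern.** The arms differ only while the patient is in Critical Care. Under Study intervention, the control arm is held to at most 30 minutes of active exercise and the intervention arm has a daily target of 90 minutes. After transfer, both arms get the same ward physiotherapy. Critical Care discharge is therefore the end of the treatment contrast, and staff on the unit are likely to know which regimen a patient has had.

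The Rivermead and FIM are scored by an observer, and dynamometry depends partly on how hard the patient is encouraged. BMI is much less exposed. If the scorer knows the arm, a between-arm difference at this visit may partly reflect scoring.

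Two uses of the data are at stake. One is the comparison at Critical Care discharge itself, including a secondary outcome that has no other reading. The other is the longitudinal comparison, because the Objective section asks about the speed of recovery as well as its extent, and the first reading of FIM, grip and quadriceps strength is the unprotected one.

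**Working it through.** No figure in the plan needs reproducing. The check sets the Blinding section against Table 1 and the Statistical analysis section.

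**Step 1. Coverage of the stated blind** (visits from Table 1; blinded visits from the Blinding section)

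| Measure | Critical Care discharge (not listed as blinded) | Hospital discharge (blinded) | 3 months (blinded) | 6 months (blinded) | Readings covered |
|---|---|---|---|---|---|
| Modified Rivermead | X | | | | 0 of 1 |
| FIM | X | X | X | X | 3 of 4 |
| Grip strength | X | X | X | X | 3 of 4 |
| Quadriceps strength | X | X | X | X | 3 of 4 |
| BMI | X | X | X | X | 3 of 4 |
| SF-36 and EQ-5D | | X | X | X | 3 of 3 |
| 6-minute walk | | X | X | X | 3 of 3 |

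All five measures at Critical Care discharge fall outside the list. The primary outcome (SF-36 physical summary at 6 months) and the walk test fall wholly inside it.

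**Step 2. Where the unprotected readings enter the analysis**

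- FIM and grip: named for a between-arm comparison at Critical Care discharge, and part of the longitudinal analysis.
- BMI: the same, but hardly open to scoring bias.
- Quadriceps: not named for comparison at this visit, so its first reading enters only through the longitudinal analysis.
- Rivermead: a listed secondary outcome but not named in the Statistical analysis section. With one reading it cannot enter a longitudinal model.

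**Step 3. What a scoring difference would do**

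Let d0 be the true between-arm difference at Critical Care discharge and d6 that at 6 months. Let b be any systematic scoring difference between arms at the unprotected visit, of either sign.

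- Contrast at Critical Care discharge: d0 + b.
- Difference between arms in change from that visit to 6 months: d6 − (d0 + b) = (d6 − d0) − b.
- Arm difference averaged over four visits with equal weight and complete data: shifted by (b + 0 + 0 + 0)/4 = b/4.
- Any contrast using only hospital discharge, 3 months and 6 months: b does not appear, provided the blind holds.

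The plan does not specify a change score. The second line shows how b would enter any arm-by-time comparison that uses the first visit as its reference. The documents give no value for b, so these lines show where a bias would go, not how large it is.

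**The case against.** The strongest reply is that the article is silent on who scores this visit, and silence is not evidence of unblinded scoring. The wording in Data collection is the article's ordinary first-person voice. A condensed article may leave the assessor's identity to the full protocol. The Blinding section is also open about which visits are protected, and the list of limitations admits that healthcare providers are not blinded.

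Part of this stands. A reader might infer that the treating physiotherapists will score the visit. The documents do not say so: Data collection gives them the session records, not the outcome scoring. What does not stand is that the gap is merely omitted detail. The Blinding section declares staff unblinded in general and then lists the exceptions, and Critical Care discharge is not among them.

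Other stronger readings also fail:

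- **That the trial's main result is at risk.** The 6-month primary outcome is among the visits given to the blinded nurse.
- **That the bias favours the intervention arm.** Neither its sign nor its size can be taken from the documents.
- **That a physiotherapy effect is most likely to show at this visit.** The article gives no basis for that. The earlier trials with a functional benefit, as described in its Background, showed it at hospital discharge, which is a blinded visit here.
- **That Rivermead distorts the longitudinal analysis.** It is measured once and cannot.

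There are fair objections to heavier remedies too. Recruitment ended on 4 December 2014 (Trial status), so blinding this visit prospectively could help few participants, if any. Giving it to the nurse who does the later assessments could unblind that nurse. Making hospital discharge the start of the main longitudinal analysis would drop the reading nearest the end of the allocated treatment.

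**Conclusion.** The point holds in a limited form. As written, the stated blind does not protect the Critical Care discharge assessments: the only Rivermead reading and one of four readings each of FIM, grip and quadriceps strength. The plan still compares FIM and grip between arms at that visit and combines this reading with three blinded ones in the longitudinal analysis. Results for these secondary outcomes, and conclusions on the rate of recovery drawn from them, are open to assessor bias of unknown size and direction.

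This rests on two assumptions: that the list of blinded visits means what it says, and that observer-scored and effort-dependent measures can be influenced by a scorer who knows the arm. If the Critical Care discharge assessor was in fact blinded, one sentence to that effect settles the matter. It is a cheap improvement to secondary analyses and no threat to the primary conclusion.

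**What to change.** 1. State who assessed participants at Critical Care discharge and whether that person was blinded to arm.
2. Unless the assessor was blinded, report the Rivermead and the Critical Care discharge results for FIM, grip and quadriceps strength as unblinded.
3. Keep the planned longitudinal analysis over all visits. Add a sensitivity analysis restricted to hospital discharge, 3 months and 6 months, and draw rate-of-recovery conclusions only where the two agree. Disagreement would not prove bias, since a true early difference could also produce it; it would mean that the data cannot separate the two.
4. For any Critical Care discharge assessment still to be done, use an assessor not involved in treatment and without sight of the physiotherapy record, where existing staff allow.

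Items 2 and 3 can go into the statistical analysis plan, which the article says will be agreed before the data are analysed. The cost is one extra analysis with fewer time points and more cautious wording for these secondary outcomes.

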### Data collection

The study data collected at each time point are summarised in table 1. All participating units contribute data to the Intensive Care National Audit and Research Centre (ICNARC) case mix programme. Data collected routinely by units as part of this national audit will be used to provide demographic, diagnostic and severity of illness data for participants. These data will include: age; gender; admission diagnoses; Acute Physiology and Chronic Health Evaluation (APACHE) II severity of illness score; number of organ failures; admission and discharge location; length of stay (in Critical Care and in hospital); status on hospital discharge; and ultimate discharge location. An estimate of each participant's premorbid functional ability (Katz's ADL Index) will be made by interview with their next of kin. For each day a participant remains in Critical Care, we will record the type and total dose of sedatives and the total calorie intake received as enteral or parenteral nutrition. Data related to each physiotherapy session will be collected by the physiotherapist allocated to that session, under the supervision of the research physiotherapist. We will assess participants at discharge from Critical Care against the Modified Rivermead Mobility Index. At hospital discharge, 3 and 6 months after study enrolment, patients will be invited to attend a follow-up appointment where the study assessments will take place. Where feasible, appointments will coincide with routine clinical follow-up, to enhance the likelihood of good compliance. Participants who do not attend their appointment will be followed up by telephone.

### Data management

To preserve confidentiality, all participants will be allocated a unique study identifier, which will be used on all case report forms and questionnaires. To allow for the possibility that the incorrect unique study identifier is recorded, the participant's initials will also be recorded on each case report form and questionnaire. Only a limited number of members of the research team will be able to link this identifier to patient-identifiable data, which will be held on a password-protected data base. All study documentation will be held in secure offices. Data management will be undertaken using a Microsoft Access database for data entry and processing, allowing a full audit trail of any alterations made to the data postentry. Original case report forms, questionnaires and consent forms will be archived securely at The Newcastle upon Tyne Hospitals NHS Foundation Trust's archive facility for 5 years following publication of the last paper or report from the study. Data will be handled, computerised and stored in accordance with the Data Protection Act 1998. No patient-identifiable data will leave the study sites. The quality and retention of study data will be the responsibility of the Chief Investigator. All study data will be retained in accordance with the latest Directive on Good Clinical Practice (2005/28/EC).

### Trial registration

In keeping with Good Clinical Practice, the study underwent all ethical requirements and applications for registration prior to the start of recruitment to the study. Application for registration of the trial via the National Institute for Health Research Integrated Research Application System was submitted on 30 June 2011, but due to a delay in administration, the trial did not appear on the registry until 20 February 2012, shortly after the start of recruitment. At this particular time, a system which automatically registered National Institute for Health Research-funded studies via the IRAS system was not in place. All legal ethical requirements were in place prior to the start of recruitment.

## Analysis

### Statistical analysis

The PCS component of the SF-36 at 6 months following recruitment is the primary end point of the study. In order to test the primary hypothesis of no difference between the intervention and control groups, the principal analysis will examine the difference between the groups on this measure using Analysis of Covariance (ANCOVA) in order to adjust for the effects of covariates in the analysis. The normality of the outcome variable will be assessed and, if necessary, transformations considered although ANCOVA are robust to deviations from this distribution. The covariates to be considered will include stratification variables (unit, admission type and preadmission activity level) in addition to demographic variables such as age and gender. More basic illustrative analyses using the t test or non-parametric alternatives may also be undertaken while, in addition, summary statistics will be calculated.

A broadly similar approach will be used to analyse the secondary outcome measures (the MCS component of the SF-36, the 6 min walk test, FIM, grip strength, quadriceps strength and body mass index (BMI)) at both 3 and 6 months post-study entry, in addition to at hospital discharge. Additionally, the 3-month and hospital discharge data on the PCS component of the SF-36 will be analysed in this fashion, along with the FIM, grip strength and BMI outcomes at Critical Care discharge. Repeated measures methods (again based on analysis of variance) will be employed in order to examine these outcome measures longitudinally across collected time points. Standard survival data methods, such as Kaplan-Meier and the log rank test, will be used to compare survival between the groups at 3 and 6 months. We will also compare durations of Critical Care and hospital stay, in addition to the delirium and ventilator-free days measures.

There are no planned interim analyses or stopping rules. An allowance for loss to follow-up has been included in the sample size calculation; data with missing observations due to loss to follow-up, as opposed to mortality, will be examined to determine both the extent of missing data and whether data are missing at random or are informative. If data are missing to a sufficient extent, the use of appropriate imputation techniques will be considered to allow for this in the analysis. All analyses will initially be performed on an intention-to-treat basis, although it may be useful to consider additional per-protocol analyses. We may base an analysis on groups defined by a dichotomisation (into long or short) length of stay in Critical Care, in addition to considering other subgroup analyses. A statistical analysis plan will be written and agreed by the Trial Oversight Committee (TOC) before analysis of the study data.

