**Methods and analysis:**

308 adult patients who have received more than 48 h of non-invasive or invasive ventilation in Critical Care will be recruited to a patient-randomised, parallel group, controlled trial, comparing two intensities of physiotherapy. Participants will be randomised to receive either standard or intensive physiotherapy for the duration of their Critical Care admission. Outcomes will be recorded on Critical Care discharge, at 3 and 6 months following initial recruitment to the study. The primary outcome measure is physical health at 6 months, as measured by the SF-36 Physical Component Summary. Secondary outcomes include assessment of mental health, activities of daily living, delirium and ventilator-free days. We will also include a health economic analysis.

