**Figure 4 BMJOPEN2015008035F4:**
[figure not shown]
Strengthening programme algorithm.

The control group will receive the standard intensity of physiotherapy which is normally given on participating units. This will consist of no more than 30 min of active exercise comprising: functional retraining (figure 3) and, if time permits, an individually tailored exercise programme, based on a muscle-strengthening algorithm (figure 4). Physiotherapy will occur from Monday to Friday as there is no physiotherapy service available routinely at weekends.

The intervention group will receive an augmented programme with a target delivery of 90 min of active exercise per day, again from Monday to Friday. The physiotherapy sessions will consist of functional retraining (figure 3) and an individually tailored exercise programme, based on a muscle-strengthening algorithm (figure 4). The delivery of this treatment will be divided into one or more sessions depending on: the individual participant's tolerance of the programme; the need for other medical and nursing interventions; and the progression of the participant's recovery.

During the physiotherapy sessions, participants will be monitored closely, and if any of the following occur, the session will be stopped: MAP <60 mm Hg; heart rate <40 or >130 bpm; oxygen saturation <88% (or, if known respiratory disease, a 10% decrease from normal oxygen saturation); marked ventilator asynchrony; participant distress; new arrhythmias; myocardial ischaemia; concern for airway integrity; endotracheal tube removal; fall to knees; or any other significant event where the participant is unable to continue rehabilitation.

Apart from the difference in the intensity of physiotherapy, both groups will have the usual rehabilitation pathway in participating units.

Following discharge from Critical Care, both groups will receive the same, standard intensity of ward-based physiotherapy, and continue with their rehabilitation pathway. In line with NICE guidance, participants will receive an exercise diary to continue independently on discharge from hospital. Any patient readmitted to Critical Care will receive standard physiotherapy care during the second and any subsequent readmissions. All readmissions will be recorded.

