Quad strength, both legs			X	X	X	X
Body mass index			X	X	X	X
Modified Rivermead Mobility Index			X			
Patient costs questionnaire						X

APACHE, Acute Physiology and Chronic Health Evaluation; SF-36, Short Form 36 Health Survey.

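### BMI is compared between arms at four visits but has no scheduled pre-treatment value, so the models lose precision and change from randomisation cannot be described

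*Protocol article*

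**What the plan says.** The Statistical analysis section treats BMI as a secondary outcome. It lists "the 6 min walk test, FIM, grip strength, quadriceps strength and body mass index (BMI)) at both 3 and 6 months post-study entry", adds hospital discharge in the same sentence, and then includes a fourth visit: "along with the FIM, grip strength and BMI outcomes at Critical Care discharge". The method is the one used for the primary outcome: "A broadly similar approach will be used to analyse the secondary outcome measures". A repeated-measures analysis over the collected time points is also planned. On covariates the section says: "The covariates to be considered will include stratification variables (unit, admission type and preadmission activity level) in addition to demographic variables such as age and" (the final item, cut off here, is gender).

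In Table 1 the row "Body mass index" is blank under Randomisation and under Rehabilitation sessions. It is marked at Critical Care discharge, hospital discharge, 3 months and 6 months.

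On the timing of treatment, the abstract says: "Participants will be randomised to receive either standard or intensive physiotherapy for the duration of their Critical Care admission". The Study intervention section adds: "Following discharge from Critical Care, both groups will receive the same, standard intensity of ward-based physiotherapy".

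Under Data collection, the national audit data "will be used to provide demographic, diagnostic and severity of illness data for participants". The items then named include age, gender, diagnoses, APACHE II score, organ failures, locations and length of stay. BMI, height and weight are not among them.

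**The concern.** BMI differs widely between people and would be expected to track within a person, so a value taken before allocation is normally the most useful covariate for a later BMI. The schedule provides none. The value at Critical Care discharge cannot take its place, because it follows the randomised treatment and may be affected by it. Adjusting for it could remove part of any effect.

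There are two consequences. The BMI comparisons are less precise than they could be, and nobody can describe how much weight was lost or regained since randomisation. The second matters more because roughly half of those randomised are expected to be assessed at 6 months. Without a starting value, one cannot see whether the assessed survivors in the two arms began at similar BMI.

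Most other outcomes without a baseline (SF-36, walk test, strength) need a cooperative patient. Height and weight do not, so for BMI the gap was more readily avoidable.

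**Working it through.** **1. The plan's own figure.** The only sample size is for the SF-36 PCS: difference 5, SD 11, power 80%, significance level 0.05 (taken as two-sided). The normal approximation gives 2 × (1.960 + 0.842)² × 11² / 5² = 76 per arm, and the t-test calculation gives 76.95, that is, 77. Allowing 40% mortality plus 10% other loss, 154 / (1 − 0.50) = 308. Both stated figures reproduce and neither is in dispute. The article gives no SD, effect or correlation for BMI.

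**2. Schedule against analysis.** BMI is analysed at four visits. It is scheduled at those same four visits and at none before or during treatment. Table and text agree, so this is not a misread table row.

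**3. Effect of a baseline covariate.** If r is the correlation between baseline and follow-up BMI, ANCOVA multiplies the variance of the arm difference by 1 − r² and the interval width by √(1 − r²). Other covariates are already planned, so r is best read as the correlation remaining after them. The range is assumed and starts at 0.5 because admission weights may be estimated or raised by fluid.

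| Assumed r | Variance × (1 − r²) | Width × √(1 − r²) | Cut in width | Equivalent sample, 1/(1 − r²) |
|---|---|---|---|---|
| 0.5 | 0.75 | 0.866 | 13% | 1.33 |
| 0.7 | 0.51 | 0.714 | 29% | 1.96 |
| 0.8 | 0.36 | 0.600 | 40% | 2.78 |
| 0.9 | 0.19 | 0.436 | 56% | 5.26 |

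**4. Detectable difference.** With 77 assessed per arm, the difference detectable at 80% power without a baseline is (1.960 + 0.842) × √(2/77) = 0.45 SD. Multiplying by the width factors gives 0.39, 0.32, 0.27 and 0.20 SD.

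**5. In BMI units, for illustration.** Assume an SD of 6 kg/m² (not in the documents). The standard error is 6 × √(2/77) = 0.967 and the 95% half-width is 1.976 × 0.967 = 1.91 kg/m². Multiplied by the factors above, the half-width becomes 1.65, 1.36, 1.15 and 0.83 kg/m². The proportional gain does not depend on the SD. The 77 may be optimistic for BMI, because participants who miss the visit are followed up by telephone, which gives no measured weight.

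**The case against.** The strongest reply is that nothing here is invalid. Allocation is randomised 1:1, so starting BMI is balanced in expectation, and the standard error of an unadjusted comparison already allows for chance imbalance. The plan compares levels and proposes no change-from-baseline analysis. All of this stands. A reader might infer that the BMI contrast is biased, or mainly reflects who was heavy on admission. The documents do not support that: variation between individuals widens the interval but does not shift the expected difference between arms.

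A reader might also infer that the comparison is too imprecise to show any plausible effect. The article states no plausible BMI effect, so there is nothing to set the interval against. At r = 0.5 the gain from a baseline is modest.

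The covariate list is open-ended, and a statistical analysis plan is to be agreed before analysis, so the choice of model could be left to it. That is fair for the model, but such a plan cannot adjust for a value that was never collected. The article is also a condensed account. The audit list is introduced as what the data will include, and Table 1 has an undetailed demographic and diagnostic row at randomisation, so height and weight may be held somewhere. Nothing shown says they are.

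Finally, BMI is peripheral. It does not appear in the list of secondary outcome measures, only in Table 1 and the Statistical analysis section. This keeps the point minor.

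**Conclusion.** The point holds as a small, inexpensive improvement. As scheduled, the BMI models cannot adjust for pre-treatment BMI, and change from randomisation cannot be described. Change from Critical Care discharge can be derived, but its starting point comes after treatment. The missing baseline does not itself bias the comparison between arms; deaths and losses are a separate matter that it leaves harder to examine.

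The cost is an interval about 1.15 times (r = 0.5) to 2.3 times (r = 0.9) as wide as it would be with adjustment, from 1/0.866 and 1/0.436. This rests on an assumed range of correlations, so the true loss is unknown. The primary outcome, its analysis and the sample size are unaffected.

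**What to change.** List BMI in the Randomisation column of Table 1, derived from admission height and weight and marked measured or estimated. The Trial status section gives the last recruitment date as 4 December 2014, so new measurement is no longer possible. What remains is to retrieve height and weight from existing admission records, by staff blind to allocation.

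Before analysis, name baseline BMI as a covariate in every BMI model, and add a sensitivity analysis restricted to measured values. Where records do not exist, report BMI as a descriptive comparison of levels only, with no statement about change since admission.

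The cost is a little data retrieval and one covariate. Estimated or fluid-affected weights will reduce the gain in precision, but they do not bias the comparison provided they were recorded before allocation.
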